## Methods

We will perform an observational controlled study at the University of Oxford and report findings according to STROBE [41]. Participant recruitment began in February 2022, and both recruitment and data collection are scheduled for completion in September 2029. Results will follow in the subsequent year.

### Study participants

Healthy: adults (≥16 years) without risk factors or clinical features of peripheral neuropathy.

Patient participants: adults (≥16 years) with risk factors for neuropathy (for example diabetes), symptoms suggestive of neuropathy, or a diagnosis of diabetic or non-diabetic peripheral neuropathy, including small-fibre neuropathy, established by clinical assessment and investigations. Also included are patients (or their first-degree relatives) with clinical features or a confirmed diagnosis of paroxysmal extreme pain disorder, familial episodic pain syndrome, erythromelalgia, or congenital insensitivity to pain.

Exclusion criteria: pregnancy; insufficient English or impaired capacity preventing informed consent or completion of questionnaires; severe psychiatric illness; significant pain from other causes that would confound assessment; central nervous system lesions likely to complicate somatosensory testing; or any other reason the investigator deems the participant unsuitable.

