#### Planned primary analysis.

Between-group comparisons (neuropathic pain vs no neuropathic pain) will be conducted using appropriate non-parametric tests (Mann–Whitney U test) where data are not normally distributed, or independent-samples t-tests where normality is satisfied.

Data from individual nociceptive fibres will be analysed with explicit consideration of clustering within participants. Where appropriate, fibre-level measurements will be summarised at the participant level (for example, by averaging) to provide an independent observation per participant for primary analyses. In addition, mixed-effects models will be used, with participant included as a random effect, to account for within-participant variability. Multiplicity arising from multiple outcomes will be addressed using appropriate multiple-comparison adjustments (for example, Bonferroni or false discovery rate correction).

This dual approach allows us to perform conservative primary analyses at the participant level by averaging, while also utilising more sophisticated modelling through a mixed-effects model that retains the detail of the individual fibre data while correcting for the dependence between fibres from the same participant. The mixed-effects model will bridge the participant (unit of inference) and individual fibre (unit of observation) without the statistical error of treating fibres from the same person as independent data points.

Multivariable logistic regression models will be used to examine the association between neuropathic pain status and microneurography-derived measures of axonal excitability and properties, adjusting for prespecified covariates (age, sex, diabetes status, neuropathy severity, and medication use).

Multicollinearity among predictors will be evaluated using variance inflation factors; when two predictors are highly correlated, the variable with greater variance or stronger biological relevance will be retained in the final model.

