#### Secondary analyses.

Secondary hypotheses explore relationships between somatosensory phenotype (QST clusters), genetic variants and nociceptor excitability signatures.

1. Somatosensory subgroup correspondence

- Compare microneurography variables across QST-defined phenotypic groups (sensory loss; mechanical hyperalgesia; thermal hyperalgesia) using non-parametric ANOVA (Kruskal–Wallis) or one-way ANOVA as appropriate.

- If omnibus tests are significant, perform post-hoc comparisons with correction for multiple testing.

2. Genetic variant effects

- Compare microneurography measures between participants who carry rare variants in ion channel genes (NaV, TRPA1) and those who do not, stratified by aetiology (diabetic versus non-diabetic).

- Use regression models to estimate the effect of genetic variants on fibre excitability, adjusting for confounders. If sample sizes for specific variants are small, present descriptive statistics and cautionary interpretation.

3. Microneurography association analyses

- Spearman rank-order correlations will evaluate associations between microneurography measures and clinical metrics: spontaneous pain intensity, evoked pain intensity, DN4/NPSI descriptor scores, and quality-of-life measures.

- A binomial regression model will examine the association between microneurography variables and membership of somatosensory subgroups.

Dimensionality reduction and clustering

Given the high dimensionality of clinical, genetic, microneurographic and biochemical data, we will use dimensionality reduction and unsupervised clustering to identify latent patient subgroups.

- Apply principal component analysis to standardised variables across the domains of interest (genetics, demographics, microneurography, biochemistry). Retain components that explain an adequate cumulative variance (e.g., eigenvalues >1).

- Apply k-means, centroid and hierarchical clustering on retained principal components. Determine optimal cluster number using multiple metrics (gap statistic, silhouette width, elbow method).

- After cluster assignment, compare original variables across clusters using omnibus tests with post-hoc comparisons to characterise cluster profiles.

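### Relatives may be enrolled, but no analysis allows for family: standard errors in the carrier versus non-carrier comparison can be wrong, most likely too small if enrolled relatives share the variant

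*Protocol article*

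**What the plan says.** Under Study participants, the protocol article widens eligibility beyond neuropathy to four named syndromes, erythromelalgia among them: "Also included are patients (or their first-degree relatives) with clinical features or a confirmed diagnosis of" one of these. No rule restricts enrolment to one person per family.

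Under Planned primary analysis, fibre data are averaged within a person "to provide an independent observation per participant for primary analyses". The accompanying mixed models are fitted "with participant included as a random effect, to account for within-participant variability". Risk of bias and mitigation again refers only to variability within a participant, and relatedness is not among its listed sources of bias.

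Under Secondary analyses, item 2, the plan is to "Compare microneurography measures between participants who carry rare variants in ion channel genes (NaV, TRPA1) and those who do not, stratified by aetiology" (diabetic or not). The model is given as: "Use regression models to estimate the effect of genetic variants on fibre excitability, adjusting for confounders". No clustering level is named there, whether fibre, participant or family. The item ends with a fallback: "If sample sizes for specific variants are small, present descriptive statistics and cautionary interpretation".

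**The concern.** The article takes up dependence explicitly, sets the level at which it will be handled, and stops one level below what its own eligibility text allows. Relatives share genes and environment beyond the variant under test, so their C-fibre measures may be correlated after carrier status is accounted for. A participant random effect, or one average per participant, does not remove that correlation.

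Secondary hypothesis 2 is at stake: it expects genetic variants to confer a distinctive excitability signature. If carriers are concentrated in a few families, a family resemblance could be reported as a variant effect with an interval that is too narrow. The Introduction links rare variants in nociceptor channels (TRPA1 and NaV subtypes) to extreme pain syndromes, and the carrier comparison concerns the same genes. Affected relatives would therefore often be carriers together.

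**Working it through.** The article states no sample size, power or standard error for the variant comparison, so there is no figure of its own to reproduce. It also gives no number of families, relatives or carriers, and no within-family correlation. Everything below rests on assumed inputs.

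**Inputs (assumed).** Family size m = 2 to 4. Residual within-family correlation ρ = 0.3 to 0.5. Carriers/non-carriers n1/n0 = 20/20, 20/80 and 12/136. Outcome variance is 1, with one summary value per participant. Tests are two-sided at 0.05, with critical value 1.96.

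**Case A: enrolled relatives are all carriers, non-carriers are unrelated.**

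- The design effect for the carrier mean is D = 1 + (m − 1)ρ. Low end: 1 + 1 × 0.3 = 1.3. High end: 1 + 3 × 0.5 = 2.5.
- The ratio of true to naive variance of the difference is R = (D/n1 + 1/n0) / (1/n1 + 1/n0).
- The standard error factor is √R, and coverage is 2Φ(1.96/√R) − 1.

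For 20/20 the two variance terms have equal weight. R = (1.3 + 1)/2 = 1.15 gives √R = 1.07, and R = (2.5 + 1)/2 = 1.75 gives √R = 1.32.

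For 20/80, R = (1.3 × 0.05 + 0.0125)/0.0625 = 1.24 and R = (2.5 × 0.05 + 0.0125)/0.0625 = 2.20.

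For 12/136, 1/n1 = 0.0833 and 1/n0 = 0.00735, so R = (0.1083 + 0.00735)/0.0907 = 1.28 and R = (0.2083 + 0.00735)/0.0907 = 2.38.

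| Carriers/non-carriers | SE factor, low to high | Coverage of nominal 95% |
|---|---|---|
| 20/20 | 1.07 to 1.32 | 93% to 86% |
| 20/80 | 1.11 to 1.48 | 92% to 81% |
| 12/136 | 1.13 to 1.54 | 92% to 80% |

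With a weaker correlation of 0.1 and families of 2 or 3, the factor is only 1.03 (20/20, pairs) to 1.09 (12/136, families of 3).

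**Case B: discordant pairs, one carrier and one non-carrier relative.**

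- R = [1/n1 + 1/n0 − 2ρ·min(n1, n0)/(n1·n0)] / (1/n1 + 1/n0).
- 20/20, ρ = 0.5: (0.1 − 0.05)/0.1 = 0.5, so √R = 0.71 and the actual type I error is about 0.006.
- 12/136, ρ = 0.1: (0.0907 − 0.00147)/0.0907 = 0.984, so √R = 0.99 and the actual type I error is about 0.048.

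Here the naive standard error is too large.

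**Check by simulation (20,000 t-tests per setting, 20/20, pairs, ρ = 0.3).** Case A: type I error 0.069, against 0.068 by formula. Case B: 0.020, against 0.019.

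With one member per family, R = 1 and the problem disappears.

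**The case against.** The strongest reply is that nothing shows the problem will arise. The eligibility phrase may admit a relative instead of the patient, and it does not settle whether relatives must themselves be affected. Recruitment is described through clinics, primary care, advertisements and earlier cohorts, with no mention of families. The Introduction also links variants in the same genes to diabetic and small-fibre neuropathy, so many carriers may be unrelated. Small groups for a specific variant are only described, so no test would be distorted there. The article is condensed, and a full analysis plan could contain a family term.

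Much of this stands, and it limits the point. It does not remove it. No text prevents several relatives from entering. The descriptive fallback covers specific variants, while the overall carrier comparison and its regression remain inferential, and the Statistical plan calls for 95% confidence intervals. The independence of participants is asserted in the article itself.

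Three stronger readings are tempting and are not supported:

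- A reader might infer that the standard errors are certainly too small. That needs several enrolled members per family, positive residual correlation, and carrier status mostly shared within families. Case B shows the sign reversing. Sharing the variant is not in itself residual correlation, because carrier status is the effect being estimated.
- A reader might apply the design effect of 1.3 to 2.5 directly, giving a factor of 1.14 to 1.58 and coverage of 91% to 79%. That describes the carrier mean alone, not the difference that will be tested.
- A reader might say that the genetic model clusters by participant only. The participant random effect is stated for the primary analysis. The genetic regression names no level at all.

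**Conclusion.** The point holds in conditional form. Relatives are eligible, participants are treated as independent, and no family term appears anywhere in the article. Once related participants are analysed together, standard errors in the carrier comparison can be wrong in either direction. Understatement is the likelier error if enrolled relatives are themselves affected and so tend to share the variant. On the Case A assumptions, the correct standard error is about 1.07 to 1.54 times the naive one, with coverage of about 93% down to 80%. The upper end needs large families, strong correlation, every carrier in such a family, and few carriers relative to non-carriers. The comparison is secondary, but the gap bears directly on secondary hypothesis 2 and is worth closing.

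**What to change.** Record a family identifier for every participant. Recruitment runs to September 2029, so this can be collected prospectively, and for those already enrolled as far as records allow.

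In the variant analysis, and in any other analysis that includes relatives, add a family random intercept with participant nested in family, or use family-clustered standard errors with a small-sample correction. State the clustering level for the genetic regression. Report the number of families contributing to each variant. Add a sensitivity analysis with one member per family.

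Where a variant occurs in only one or two families, keep the article's descriptive reporting, because no model can then separate family from variant.

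The cost is one data field and a few lines of analysis text. Intervals for variant effects will usually widen, and with few families the family variance will be poorly estimated, which is why the sensitivity analysis and the family counts are needed.

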### Study participant recruitment

Participants will be recruited from multiple sources to capture broad neuropathy and pain severity spectra: specialist neuropathy and clinical neurophysiology clinics, diabetic podiatry clinics, primary care networks such as the Thames Valley Primary Care Research Partnership, advertisements, and previous study cohorts where consent permits recontact.

### Ethical approval and consent to participate

Ethical approval was obtained from the South Central – Oxford C Research Ethics Committee (18/SC/0263). All participants will provide informed written or electronic consent in accordance with the Declaration of Helsinki. Adverse events during microneurography or other study procedures will be recorded. Protocol amendments will be approved by the ethics committee, registered and communicated to collaborators.

### Tools for phenotyping and study procedures

Patient participants will undergo a deep clinical phenotyping [42] and then divided into groups based on aetiology, neuropathy, and neuropathic pain grading [10].

The tools for phenotyping and study procedures closely align with the DOLORisk protocol, which incorporates questionnaires, clinical assessments, and specialised investigations.[42]

### Questionnaires

#### Demographic and lifestyle information.

The study records demographic information, including age, gender, weight, height, and smoking and alcohol consumption.

#### *Characterisation of pain – pain location, intensity, quality, analgesics*.

We assess the presence and duration of pain, including dysaesthesia. Participants are asked to indicate where they feel pain on their body using a list of body sites and a body map. They identify all areas where they have experienced pain over the past three months and mark the location that bothers them the most.

Pain intensity is measured using different scoring systems such as the Chronic Pain Grade [43] over the past three months and the Brief Pain Inventory [44]. An additional item asks about the average pain experienced over the past seven days. Pain descriptors are characterised by the DN4 (*Douleur Neuropathique en 4 questions*) [45], and the Neuropathic Pain Symptom Inventory [46]. These questionnaires use an 11-point numerical scale to quantify severity of pain and symptoms.

The Michigan Neuropathy Screening Instrument is a screening tool for diabetic neuropathy and asks participants about symptoms related to diabetic neuropathy, such as pain, numbness, tingling, and loss of sensation in the feet and legs [47].

We record details of pain medication (e.g., paracetamol, gabapentin), dose, analgesic relief, and adherence to medication.

#### Pain interference, quality of life and psychological variables.

The Patient-Reported Outcomes Measurement Information System (PROMIS) questionnaires are used to assess several psychological and psychosocial variables [48]. These include depression, anxiety, sleep disturbance, fatigue and pain interference. Other psychological questionnaires include Ten-Item Personality Inventory [49], and assessments of Pain Related Worrying [50] and State Optimism Measure [51].

The EQ-5D [52] measures quality of life with a visual analogue scale and five items evaluating the impact of pain on the ability of the participant to perform everyday tasks.

### Clinical neurological assessment

A comprehensive structured upper and lower limb neurological examination is performed to detect clinical signs of a peripheral neuropathy. The examination includes assessment of muscle bulk, tone, motor power, deep-tendon reflexes (using a Queen square tendon hammer). The sensory examination assesses vibration perception (using a 128 Hz tuning fork), pinprick sensation (using ‘Neurotip’), temperature (using Somedic RollTemp, Somedic AB, Sweden), light touch (using 10g monofilament) and, joint position sense.

The clinical findings for a length-dependent neuropathy are quantified with the Toronto Clinical Scoring System (TCSS) [53].

### Specialised investigations

#### Microneurography.

Microneurography records single-unit activity from peripheral sensory nerves in awake participants by inserting a microelectrode into a peripheral nerve [54]. We typically use the superficial peroneal nerve on the dorsum of the foot because it is superficial, purely sensory, anatomically relevant to distal symmetrical polyneuropathy, and generally well tolerated. It is also the most distal nerve available, which provides an advantage for length-dependent (‘dying-back’) neuropathies that show a distal-to-proximal gradient. In older participants (>70 years) or those with severe neuropathy where the superficial peroneal nerve is denervated or inaccessible, alternative sites (superficial radial nerve or more proximal peroneal sites) will be used.

C-fibres are characterised by the phenomenon of activity-dependent slowing of conduction velocity in response to repetitive transcutaneous electrical stimuli, and natural stimulation in a series of experiments [24].

The core protocol will consist of:

Identification of C-fibres at 0.25 Hz stimulation. After identification, stimulation is paused for three minutes to allow baseline recovery, followed by six minutes at 0.25 Hz. The rate is then increased to 2 Hz for three minutes and followed by a further six minutes at 0.25 Hz. The pause and 0.25 Hz blocks may be adjusted for participant tolerability, but the 2 Hz block will not be shortened.

Where possible this will be followed by the extended protocol.

Stimulation at 0.125 Hz, 0.25 Hz, 0.5 Hz and 1 Hz for at least two minutes at each frequency.Paired-pulse testing to assess recovery cycles by delivering a test stimulus at progressively shorter intervals after a conditioning stimulus.Mechanical and thermal natural stimulation of the receptive field using von Frey hairs and thermal probes (40°C, 45°C, 48°C and 20°C) to determine transduction thresholds and sensitisation to mechanical and thermal stimulation.

We aim to record from up to three independent receptive fields per participant, but a single stable recording suffices for inclusion. All C-fibres will undergo the core protocol; the extended protocol is optional and recorded whenever feasible.

C-fibre subtypes are classified according to their response to an increase in electrical stimulation frequency to 2 Hz. This response, known as activity-dependent slowing of conduction velocity, is a characteristic feature of C-fibres in which conduction latency increases (i.e., slows) following repetitive stimulation. Using this method, five distinct populations of C-fibres can be identified: type 1A (“mechano-sensitive”) nociceptors, type 1B (“mechano-insensitive”) nociceptors, cold thermoreceptors, low-threshold mechanoreceptors, and cutaneous sympathetic efferent fibres [24,25].

There are two main reasons for distinguishing between a core and an extended recording protocol. The first relates to participant tolerability. Some individuals, particularly older participants, find prolonged recordings difficult due to musculoskeletal discomfort, difficulty keeping the limb still, challenges in following instructions, or urinary urgency. To minimise discomfort, participants are seated in a supportive chair with pillows to cushion pressure points, and are offered comfort breaks at the start of the recording. The second reason concerns recording stability. C-fibre signals may be lost during longer sessions because of small movements of the electrode or limb, or loss of contact during natural stimulation. As a result, extended recordings cannot always be completed. To prevent ascertainment bias, data from the extended protocol will therefore be treated as secondary or exploratory outcomes.

Microneurography measurements will include measures of:

Axonal properties

i. Baseline conduction velocity.ii. Degree of activity-dependant slowing to several stimulation frequencies (e.g., 0.25 Hz to 2 Hz)iii. Action potential morphology analysis of the extracellular recorded action potentialsiv. Threshold responses to thermal and mechanical stimulation

Nociceptor excitability

i. Spontaneous activityii. Double or multiple spikesiii. Thermal and mechanical sensitisation defined as prolonged ongoing discharges outlasting stimulus duration or lowered thresholds in response to thermal and mechanical stimulation.

Axonal excitability (across all C-fibre types)

i. The velocity recovery cycle refers to the interval-dependent change in C-fibre conduction velocity after an action potential. It is used to measure refractoriness and excitability. It progresses through several distinct phases that depend on the time interval between the first (conditioning) action potential and the second (test) action potential. These phases include the refractory period, the supernormal period, and the late subnormal period.

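### Recording site can shift with age and neuropathy severity, but the unadjusted pain comparison ignores it and neither the mixed model as described nor the logistic covariate list includes it

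*Protocol article*

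**What the plan says.** **Where recordings are made** (Protocol article, Microneurography). The default is stated as "We typically use the superficial peroneal nerve on the dorsum of the foot". One reason given is that this is the most distal nerve available, an advantage in "neuropathies that show a distal-to-proximal gradient". The exception reads "In older participants (>70 years) or those with severe neuropathy where the superficial peroneal nerve is denervated or inaccessible"; in those cases "alternative sites (superficial radial nerve or more proximal peroneal sites) will be used". There are thus three site levels: foot superficial peroneal, more proximal peroneal, and superficial radial in the arm.

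**How the groups are compared** (Planned primary analysis). Three analyses are described:
- a t-test or Mann–Whitney test of pain against no pain on participant-level summaries, without covariates, which the section presents as the conservative primary analysis;
- a mixed model of fibre-level data, "with participant included as a random effect";
- a multivariable logistic regression, "adjusting for prespecified covariates (age, sex, diabetes status, neuropathy severity, and medication use").

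Recording site appears in none of them. The section Risk of bias and mitigation does not mention it either. It says only that regression models will adjust for confounders, and it addresses sampling bias through multiple receptive fields and mixed models.

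**The concern.** Site is not assigned at random. It moves away from the foot for reasons tied to age and neuropathy severity, and severity may well be related to pain status. The protocol's own reason for preferring the foot implies that a more proximal or arm recording samples nerve at a different point on the disease gradient. If the pain groups differ in how often an alternative site is used, part of any difference in conduction velocity, activity-dependent slowing or spontaneous activity may reflect electrode location rather than pain. The error can go either way: it can create a difference, or hide a real one if the worst-affected participants are recorded where the nerve is better preserved.

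**Working it through.** **1. Is body region handled anywhere?** Under Quantitative sensory testing, scores are normalised for age, sex and body region. Region is thus allowed for in the psychophysical measure but not in the microneurography measures that form the primary outcome.

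**2. The plan's own figure.** Under Sample size justification the regression model has 8 degrees of freedom at 15 per degree of freedom: 8 × 15 = 120, as stated.

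**3. Expected recordings.** From the recruitment target and the stated minimum success rates: 0.60 × 124 + 0.80 × 148 = 74.4 + 118.4 = 192.8, about 193. The protocol does not give the split by pain status. An equal split is assumed, about 96 per group.

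**4. Bias of the unadjusted comparison.** Bias = (difference in alternative-site share between pain groups) × (site effect in SD). The protocol gives neither factor, so both are assumptions: shares differing by 10 or 20 points, site effects of 0.5 or 1.0 SD.

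The type I error is for a two-sided 5% test with no true pain effect, by normal approximation. SE = √[(2/96) × (1 + s² × 0.2 × 0.8)], where s is the site effect and the last term is the variance that site adds if about 20% of recordings are at alternative sites (assumption).

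| Share difference | Site effect | Bias | SE | Type I error |
|---|---|---|---|---|
| 0 | any | 0 | – | 5% |
| 10 points | 0.5 SD | 0.05 SD | 0.147 | 6.3% |
| 10 points | 1.0 SD | 0.10 SD | 0.155 | 9.9% |
| 20 points | 0.5 SD | 0.10 SD | 0.147 | 10.4% |
| 20 points | 1.0 SD | 0.20 SD | 0.155 | 25.1% |

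Leaving out the added site variance gives 6.4%, 10.7%, 10.7% and about 28% in the four non-zero rows. For scale, the difference detectable with 80% power at 96 per group is (1.96 + 0.84) × √(2/96) ≈ 0.40 SD.

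**5. Does adjusting for age and severity already deal with it?** A simulation used 193 participants, 1,000 runs per setting and no true pain effect. An alternative site was used, with probability 0.6, in participants over 70 or with high severity. Pain depended on severity to varying degrees, and the site effect was 0.5 or 1.0 SD. These are assumptions. The models were linear, with the microneurography measure as outcome and one value per participant, so they show the principle rather than the planned logistic fit.
- Unadjusted: bias up to about 0.12 SD and type I error up to 12.9%, at the strongest link between pain and severity and a 1 SD site effect.
- Adjusted for age and severity, without site: bias at most 0.01 SD and type I error 3.6% to 6.5%, which is close to 5% given a simulation error of about 0.7 points.

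**6. Can a site term be afforded?** By the protocol's own rule, foot versus alternative needs 9 × 15 = 135 and three levels need 10 × 15 = 150. Both are below 193.

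**The case against.** The strongest reply is that the logistic model adjusts for age and neuropathy severity, the two stated drivers of site choice. Step 5 bears this out: if site depends only on those two and chance, the bias all but disappears. A reader might infer that site differences contaminate every planned pain comparison; the document does not support that. What the reply leaves standing is that the participant-level test has no covariates and the mixed model is described without any. The logistic model keeps some residual confounding only if nerve access relates to pain beyond graded severity, or if severity is coded coarsely.

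A reader might also infer that everyone over 70 or with severe neuropathy is moved off the foot. On its natural reading the text limits the move to those whose foot nerve is unusable, so age and severity alone do not fix how often alternative sites are used.

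Third, the article condenses a fuller plan, and its mixed-model description does not list even a pain-group term. The missing site term there is weak evidence of a decision. The logistic covariates are different: they are named and called prespecified.

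Finally, hand sensory testing is allowed for, so arm recordings could be matched to it, although matching is not required.

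**Conclusion.** The point holds as a cheap improvement to the analysis, not as a demonstrated bias. Site can change with age and severity, the protocol's own reasoning says the sites differ, and no described analysis includes it. The consequence falls mainly on the unadjusted participant-level comparison and on the mixed model as described.

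Under the assumed ranges the false difference is 0.05 to 0.20 SD, with a type I error of about 6% to 25%. This rests on an equal split of about 193 recordings and on site shares and site effects that the protocol does not report. If alternative sites are used equally often in both groups there is no bias, so confidence in the size is limited.

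**What to change.** - Add recording site (foot superficial peroneal, proximal peroneal, superficial radial) as a fixed effect in the mixed model and as a covariate in the regression models. Collapse to foot versus alternative if cells are sparse.
- Prespecify a sensitivity analysis of the primary comparison restricted to foot superficial peroneal recordings.
- For secondary hypothesis 1, pair each recording with the sensory testing result from the same body region where available.

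**Cost.** No new data are needed. The models use one or two more degrees of freedom, so the protocol's minimum rises from 120 to 135 or 150. That rule counts participants where events per variable would count the smaller outcome group. With 30% to 50% of 193 in that group there are 58 to 96 events, or 5.8 to 9.6 per degree of freedom at 10 degrees of freedom, against 7.2 to 12.1 at 8. This is a separate matter, but it favours the two-level coding if data are thin. Site will be partly collinear with severity, and the protocol allows highly correlated predictors to be dropped, so the plan should say whether that rule applies to site. The foot-only analysis will be less precise.
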